## SAP-summary of changes

Few changes were made, and while not updated in the original protocol, published protocol version and registry.

1. **Original Protocol:** We stated we will explore the role of clustering effects in the trial by performing a sensitivity analysis examining the implications of clustering by the instructor by adding an instructor random effect to our mixed-effects model.

**ANZCTR – Registration:** We will explore the role of clustering effects in the trial by performing a sensitivity analysis examining the implications of clustering by the instructor by adding an instructor random effect to our mixed-effects model.

**Open access protocol publication:** We will explore the role of clustering effects in the trial by performing a sensitivity analysis examining the implications of clustering by the instructor by adding an instructor random effect to our mixed-effects model.

**Final Manuscript:** We did not examine the role of clustering effects in the trial because more than 80% of the yoga classes were conducted by one instructor, and more than 80% of the strengthening exercise classes were conducted by another instructor.

2. **Original Protocol:** We stated we will assess the effects of potential confounders or interaction with treatment by covariates, including age, sex, BMI, disease severity, comorbidities, health status, and use of pain medications.

**ANZCTR – Registration:** We stated we will also assess the effects of potential confounders or interaction with treatment by covariates, including age, sex, BMI, disease severity, comorbidities, health status, and use of pain medications.

**Open access protocol publication:** We stated we will assess the effects of potential confounders or interaction with treatment by covariates, including age, sex, BMI, disease severity, comorbidities, health status, and use of pain medications.

**Final Manuscript:** Regarding the additional adjustments for disease severity that was initially specified in our study protocol, we were unable to include these variables in our final models due to inadequate data. However, we adjusted our model for comorbidities, health status, and use of pain medications, and the results were similar to those of the unadjusted model, so we removed it from the model.

3. **Original Protocol:** We stated “the above sample size will allow us to detect a non-inferiority of yoga with strengthening exercise. Non-inferiority would be declared if the mean change in knee pain (assessed using VAS) in the yoga group was not significantly worse than the mean change in the strengthening exercise group, within a pre-stated margin of non-inferiority ( $\Delta$ ), in this case, set at 10 mm”.

**Open access protocol publication:** We stated “the above sample size will allow us to detect a non-inferiority of yoga with strengthening exercise. Non-inferiority would be declared if the mean change in knee pain (assessed using VAS) in the yoga group was not significantly worse than the mean change in the strengthening exercise group, within a pre-stated margin of non-inferiority ( $\Delta$ ), in this case, set at 10 mm”.

**Final Manuscript:** Since our study was powered for non-inferiority and has met the criteria for switching the trial objective from superiority to non-inferiority, as outlined by the European Agency for the Evaluation of Medicinal Products (EMA 2001), we conducted a non-inferiority analysis.

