### **Randomisation and blinding:**

Allocation of participants in a 1:1 ratio to either a 12-week *yoga program* or *strengthening exercise program* will be based on computer-generated random numbers prepared by a statistician with no involvement in the trial. Code-break for the full randomisation schedule will be maintained by the administering institute.

The assessors will be blinded to treatment allocation for objective outcome measures. Allocation concealment and blinding will be ensured by having two research nurses coordinate the trial. Assessments will be taken by the research nurse blinded to the group allocation.

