### **Treatments:**

Overall, 126 eligible participants will be randomly allocated to a 24-week group-based *yoga program* or *strengthening exercise program* (each with two 1-hour group-based sessions and one 1 hour home based session per week). Group sessions will be led by physiotherapist/exercise physiologists/yoga teachers for the first 12 weeks. Trainers will lead a group of approximately 10 participants. Participants will be instructed to continue their *yoga* or *strengthening exercise* at home for another 12 weeks. Using REDCap, weekly email follow-up will be done with the participants to confirm the compliance to the home-based program, and video instructions will be given to each participant to support the home-based program.

An evidence-based *yoga program* designed by a yoga expert and researcher - [name] from the Maryland University of Integrative Health, USA will be delivered by yoga

teachers. Each yoga class will begin with a breathing exercise (*pranayama*) and chanting (10min), warm-up, and moving sequences (*asanas*, 40 min). Classes will end with deep relaxation (*savasana*) and meditation (10 min). Classes will include an application of yoga philosophy and replace negative thoughts with positive ones (*pratipaksa bhavanam*). Details about interventions are in the appendix.

The strengthening exercise therapy regimen will be designed by [name] as a group-based progressive strengthening exercise program based on those used in past clinical trials and shown to be effective. Details about interventions are in the appendix.

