**Primary outcome:**

Change in knee pain assessed by VAS for over 12 weeks. Pain will be evaluated at each time point using a 100mm VAS and asked: “On this line, how would you rate your overall average knee pain in the last one week”? For knee pain assessed using VAS, terminal descriptors will be 0mm = no pain, 100mm = worst pain possible.

**Secondary outcomes:** (overall change from baseline to week 12 and overall change from baseline to week 24 are separate outcomes)

1. Change in VAS knee pain over 12 weeks in patients with painDETECT>12
2. Change in VAS knee pain over 24 weeks.
3. Change in WOMAC knee pain, WOMAC stiffness, and WOMAC knee function over 12 weeks and over 24 weeks.
4. Change in physical function as assessed by 30s Chair Stand Test, 40m Fast Walk Test and Stair Climb Test over 12 and over 24 weeks
5. OMERACT\_OARSI responders (meeting responder criteria) at week 12, and 24 weeks
6. Change in biomarker (urinary CTX-II, serum COMP, and serum hyaluronan) and systemic inflammatory markers (hs-CRP, IL-6, TNF- $\alpha$ ) over 12, and over 24 weeks
7. Change in Patient Health Questionnaire (PHQ-9) scales over 12, and over 24 weeks
8. Change in patient global satisfaction score over 12, and over 24 weeks
9. Change in painDETECT scores over 12, and over 24 weeks
10. Change in leg muscle strength (quadriceps) over 12, and over 24 weeks
11. Change in gait speed from baseline to week 12 and baseline to 24 weeks

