***Sample Size calculation:***

Our power calculations are based on a sample size that can document the minimal clinically important difference (MCID) in VAS knee pain superior to yoga compared to strengthening exercise. Based on the MCID of 15mm in VAS pain [a numerical scale ranging from 0 (no problem) to 100 (maximum problem)], two-sided significance level of 0.05, 90% power and SD of VAS pain change 22.5, we will need a total of 98 participants. Assuming a worse scenario of 20% dropout, we will need 126 participants.

The above sample size will allow us to detect a non-inferiority of yoga with strengthening exercise. Non-inferiority would be declared if the mean change in knee pain (assessed using VAS) in the yoga group was not significantly worse than the mean change in the strengthening exercise group, within a pre-stated margin of non-inferiority ( $\Delta$ ), in this case, set at 10 mm. Overall, 126 participants will give us 80% power to detect the non-inferiority of yoga compared with strengthening exercise.

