**Data analysis:**

The comparisons of pain and other continuous outcomes will be done employing a repeated measures mixed model incorporating terms of treatment, time, and respective baseline values as covariates. We will also assess the effects of potential confounders or interaction with treatment by covariates, including age, sex, BMI, disease severity, comorbidities, health status, and use of pain medications. A two-sided p-value less than 0.05 will be considered to indicate the statistical significance, and the results will be shown as the between-group differences with 95% confidence intervals (95% CIs) of the differences.

We will explore the role of clustering effects in the trial by performing a sensitivity analysis examining the implications of clustering by the instructor by adding an instructor random effect to our mixed-effects model.

We will also perform an exploratory analysis to investigate whether the presence or absence of neuropathic pain, as assessed by the painDETECT questionnaire, is a potential moderator that influences response to treatment for the primary outcome at 12 weeks. To assess the moderation of the effect by painDETECT (binary moderator), an interaction term between the randomised group and the potential moderator will be included in outcome regression models.

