#### **1. Linear Mixed Effects Model (Repeated-measures mixed-effects model)**

We chose mixed-effects models for the primary analyses because they are well-suited to handle longitudinal data with repeated measures over time. These models account for the correlation within subjects by including random effects, which allows each participant to serve as their own control and reduces bias arising from individual differences. Moreover, mixed-effects models are flexible in accommodating missing data under the assumption that data are missing at random. Importantly, no imputation procedures for missing data were performed, as these were not pre-specified in the original study protocol.

STATA functions used: -mixed function in STATA (version 18) was used for the modelling of linear mixed effects model. The -margins command was used to calculate the estimated value of the outcome measure at each time point. The -lincom function was used to calculate the within- and between-group differences over time.

The outcomes for which we used linear mixed effects models were visual analog scale (VAS) knee pain, Western Ontario and McMaster University Index (WOMAC) subscales (pain, function, and stiffness), patient global assessment, Depression (as assessed by patient health questionnaires), quality of life derived utility values, core physical performance measures (as assessed by 30 s chair stand test, 40 m fast walk test, and stair climb test), neuropathic pain (as assessed by painDETECT questionnaire) and leg muscle strength. First, the main effects are treatment group, time, and interaction of treatment group with time. The presence of time interaction allows us to estimate the treatment effect at different time points (each follow-up). Second, the model was also adjusted for baseline values for each continuous outcome, age, sex, and BMI. Furthermore, the interaction terms for each confounder with time were added. Third, participant ID was included as a random effect allowing random intercepts. This addresses the correlation within repeated measures. Fourth, the mixed-effects model was fitted using default setting of -mixed function (independent covariance and the restricted maximum likelihood method).

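### Participants are treated in classes of about 10, but power and the fitted model assume independence; the reason given for dropping the only clustering check does not rule out correlation among classmates

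*Combined protocol and SAP*

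**What the plan says.** The protocol randomises individuals (Randomisation and blinding: "Allocation of participants in a 1:1 ratio"). It delivers both programmes in groups (Treatments: "each with two 1-hour group-based sessions and one 1 hour home based session per week"; "Trainers will lead a group of approximately 10 participants"). The led group sessions run for the first 12 weeks, which is the primary outcome window ("Change in knee pain assessed by VAS for over 12 weeks").

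The sample size sections of the protocol and SAP give 98 participants, raised to 126 for dropout, with no ICC or design effect.

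The Data analysis section of the SAP plans a single clustering check, as a sensitivity analysis: "examining the implications of clustering by the instructor by adding an instructor random effect to our mixed-effects model". The Linear Mixed Effects Model section, which describes the analysis actually used, states that "participant ID was included as a random effect allowing random intercepts". It lists no class or instructor term.

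Item 1 of the SAP summary of changes reports that the check was dropped: "We did not examine the role of clustering effects in the trial because more than 80% of the yoga classes were conducted" by one instructor, while a different instructor gave more than 80% of the strengthening classes. Item 3 reports that a non-inferiority analysis was then conducted. Its margin in the plan is 10 mm. Clustering by class is not mentioned anywhere.

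**The concern.** People who exercise together twice a week for 12 weeks share sessions, peers, a timetable and a teacher. Their pain outcomes may therefore be correlated. A participant random intercept handles repeated measurements on one person. It does nothing for correlation between people in the same class.

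The reason given for dropping the check concerns a different question. One dominant instructor per arm means that an instructor effect can hardly be told apart from the treatment effect, so the planned term was a poor tool. Classes are a separate level: there are several within each arm, and an effect at that level can be estimated whoever teaches.

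What is at stake is the standard error of the primary contrast. If it is understated, the superiority test rejects too often and the upper confidence limit falls below the non-inferiority margin too easily. The second matters more here, because the trial's objective was switched to non-inferiority.

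**Working it through.** **Inputs from the documents.** Difference 15 mm ("Based on the MCID of 15mm in VAS pain"), SD of change 22.5, two-sided alpha 0.05, power 90%, N = 98 evaluable and 126 enrolled, dropout 20%, non-inferiority margin 10 mm with 80% power claimed for 126, and about 10 participants per group.

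**Assumptions.** The class ICC is not given, so I use 0.01, 0.05 and 0.10. I assume that each participant belongs mainly to one class.

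**1. The plan's own figure.** A two-sample t-test with difference 15, SD 22.5, alpha 0.05 and 90% power needs 49 per arm, or 98 in total. The normal approximation gives 96. The stated 98 is therefore exactly an independence calculation. For dropout, 98/0.8 = 122.5, or 123. The stated 126 is close to this.

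**2. Class size at analysis.** 126/2 = 63 per arm, and 63/10 gives about 6 classes per arm. After 20% dropout, 63 × 0.8 is about 50 per arm, and 50/6 is about 8 analysed per class. Size 8 is therefore the one to pair with 50 per arm.

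**3. Consequences at m = 8.**
- Design effect: DE = 1 + (m − 1) × ICC = 1 + 7 × ICC.
- Factor by which the SE is understated: √DE.
- Two-sided type I error: 2 × [1 − Φ(1.96/√DE)]. The one-sided non-inferiority error at nominal 2.5% is half of this.
- Superiority power: noncentral t with effective n = 50/DE per arm, unadjusted change scores.
- 95% CI half-width at 49 per arm: 1.96 × 22.5 × √(2/49) × √DE.

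| ICC | DE | SE factor | Two-sided type I | One-sided (nominal 2.5%) | Power, 50 per arm | Half-width, mm |
|---|---|---|---|---|---|---|
| 0 | 1.00 | 1.00 | 5.0% | 2.5% | 91% | 8.9 |
| 0.01 | 1.07 | 1.03 | 5.8% | 2.9% | 89% | 9.2 |
| 0.05 | 1.35 | 1.16 | 9.2% | 4.6% | 81% | 10.4 |
| 0.10 | 1.70 | 1.30 | 13.3% | 6.6% | 71% | 11.6 |

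The half-widths are for a simple comparison of change. Baseline adjustment and repeated measures would narrow them, but the SE factor would still apply. They show the scale: with no clustering the interval fits inside a 10 mm margin at an observed difference of zero, and at ICC 0.05 it does not.

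**4. Non-inferiority power.** The stated 80% reproduces with one-sided alpha 0.05 and all 126 evaluable (80.2%). At one-sided 0.025 it is 70.3%. With all 126 evaluable the class size is 10, so DE is 1.09 / 1.45 / 1.90. The 80.2% then becomes 77.2% / 66.5% / 56.5%, and the 70.3% becomes 66.6% / 54.4% / 44.0%.

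**5. Few classes.** With 12 to 13 classes in total, degrees of freedom for the arm contrast are about 10 to 11. The critical value is then about 2.23 to 2.20 rather than 1.96. The table does not include this further widening.

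**The case against.** Several points on the other side stand.

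- **The ICC is unknown.** At ICC 0 nothing changes, and at 0.01 type I error rises only to 5.8%. A reader might infer that the intervals are definitely too narrow. The documents do not support that, because the size and even the presence of the effect depend on a quantity they do not report.
- **Class structure is not documented.** The plan does not say that membership was fixed, that both weekly sessions were with the same people, or how many classes ran. A third of the sessions are at home, and classes could move online. If participants mixed freely, correlation would be diluted and a strictly nested class effect would be mis-specified.
- **Instructor is not fully aliased with arm.** More than 80% is not 100%. Other instructors may have given the rest, so the confounding is near rather than complete.
- **The fitted model adjusts for baseline.** This reduces variance by a factor of (1 + r)/2 relative to change scores, where r is the correlation between baseline and follow-up. With assumed r of 0.3 / 0.5 / 0.7, m = 8 and ICC 0.05, power at 50 per arm is 94% / 90.5% / 87%. The power loss may thus be largely offset. The type I error is not, because adjustment leaves the design effect in place.
- **The change was disclosed, and clustering was only ever a sensitivity analysis.** Making a class effect primary after the fact is a post hoc change, and its variance would be estimated from about 6 classes per arm.

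These points limit the claim and the remedy. None of them makes instructor dominance a reason to leave class-level correlation unexamined.

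**Conclusion.** The concern holds in conditional form. Power and the fitted model treat participants in shared classes as independent, and the only safeguard was dropped for a reason that does not bear on correlation among classmates. If the class ICC is positive, the intervals are likely too narrow.

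With about 8 analysed per class and ICC from 0.01 to 0.10, the SE is understated by a factor of 1.03 to 1.30. Two-sided type I error is 5.8% to 13.3%, and the one-sided 2.5% non-inferiority error becomes 2.9% to 6.6%. Unadjusted superiority power is 89% to 71% against 90% stated. These figures rest on the assumed ICC, on reasonably stable class membership, and on about 6 classes per arm.

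A reader might go further and infer that the non-inferiority conclusion is wrong. The documents do not support that: they give no ICC, class count or trial estimate. What can be said is that the omitted check bears directly on a margin-based claim.

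**What to change.** 1. Refit the primary and non-inferiority models with a random intercept for class group nested within arm, above the participant level, using Kenward-Roger or Satterthwaite degrees of freedom. If people changed class, use the class they mainly attended. At the least, report this as a sensitivity analysis in place of the dropped instructor check.
2. Report the number of classes and the estimated ICC.
3. If class membership was not recorded, say so, and show the non-inferiority result over a range of assumed ICCs.
4. State that the 90% superiority power and the 80% non-inferiority power assume no clustering, and give both over an ICC range.
5. In item 1 of the SAP summary of changes, replace the rationale with a statement that instructor and arm are largely confounded, so the comparison is of each programme as delivered by its main instructor.

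The cost is one model term, somewhat wider intervals, lower stated power, and a variance component that about 6 classes per arm will estimate imprecisely. Class attendance must be retrieved. The sponsor could count classes by instructor, which suggests that class records exist, but the documents do not say that individual membership was kept.
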